## Objectives and hypothesis

### Primary objective

Evaluate whether a single session of anodic tDCS associated to sensory PES is superior to reduce pain intensity of individuals with SCD (HbSS and HbSC) compared to individual or sham use of these techniques.

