### Sample size

The sample size was calculated using the GPower software version 3.1.9.2 (Faul et al., 2007). The overall study objective is to test the hypothesis that association of anodic tDCS and sensory PES reduces pain intensity by a large percentage as opposed to use of isolated tDCS or PES in individuals with SCD. We assumed that the sample will be equally randomized into four intervention groups: (1) active tDCS + active PES; (2) active tDCS + Sham PES; (3) Sham tDCS + Active PES; and (4) Sham tDCS + Sham PES. We proceeded with the desired sample size assuming no financial or logistic limitations. The parameters used were: 80% power; 5% Type I error; effect size of 0.35 (Cohen, 1977) on the reduction of pain intensity evaluated by the VAS; four intervention groups; two genotypes (HbSS and HbSC) subgroups; and two repeated measures (pre- and post-intervention). Using these parameters yield to an estimated 64 participants for each genotype, a total *n* = 128. To increase the likelihood of achieve the computed sample size in a timely fashion, this clinical trial will be promoted through social media and posters in SCD treatment centers explaining the purpose and potential benefits of the study.

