### Statistical analysis

To ensure impartiality of the results, researchers who do not participate in any stage of data collection will perform the statistical analysis. Descriptive statistic will be used to summarize demographic and clinical sample characteristics. Shapiro–Wilk test will be performed to test normality of the data. Chi-square test will be used to compare frequency distributions and one-way ANOVA or Kruskal–Wallis *H*-test will be used to compare baseline means among the four intervention groups. The main outcome of the study is pain rating measured by the VAS. For that, we will run a repeated measure analysis of variance (ANOVA) to evaluate differences among intervention groups (active tDCS + active PES; active tDCS + Sham PES; Sham tDCS + Active PES; and Sham tDCS + Sham PES), genotypes (HbSS and HbSC), and time (pre- and post-intervention). For most of the secondary outcomes (TMS volume map; TMS center of gravity; BDNF serum level; and TNF serum level) the repeated measures ANOVA will have the same three factors listed above. Relative EEG power will further include in the ANOVA the factors ROI (frontal, temporal, central, parietal, and occipital) and EEG condition (resting, Kinesthetic–MI of painful, and Kinesthetic–MI of non-painful region of the body). All analysis will be controlled for anxiety/depression symptoms. Bonferroni test will be used to correct for multiple comparisons. An α-value of 5% (*P* < 0.05) will be used to accept statistically significant differences for all analyses.

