## Potential pitfalls and counteracting measures

This protocol was designed with the main purpose of answering the question “Does tDCS combined with PES have an additive effect in the control of osteonecrosis joint pain associated with SCD?” As in any clinical trial, risk of bias and errors exist. Several strategies will be used to reduce them:

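### The four-level group analysis with an undefined Bonferroni family names neither the combination-versus-single contrasts nor a tDCS × PES contrast, and can cost power on the main claim

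*Protocol article*

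**What the plan says.** All references are to the protocol article.

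- **Design.** Within each genotype, the Study design section crosses active or sham tDCS with active or sham PES, 16 participants per cell. That is a complete 2×2 factorial with 32 per intervention over both genotypes.
- **Analysis.** The Statistical analysis section specifies a repeated-measures ANOVA with intervention (four levels), genotype and time. For EEG power it adds region and recording condition, so it does set out the factors of each model. It has no separate tDCS and PES factors and no planned contrast. On multiplicity it says "Bonferroni test will be used to correct for multiple comparisons" and gives neither the comparisons nor their number.
- **Objective.** The Primary objective asks whether the combination "is superior to reduce pain intensity of individuals with SCD (HbSS and HbSC) compared to individual or sham use of these techniques". The first item under Hypothesis and the aim stated under Sample size also set the combination against single use.
- **Main question as worded later.** The Potential pitfalls section gives it as: "Does tDCS combined with PES have an additive effect in the control of osteonecrosis joint pain associated with SCD". The Introduction describes the combined effect as the sum of the separate analgesic effects, and also as synergistic.
- **Sample size.** The inputs are "80% power; 5% Type I error; effect size of 0.35 (Cohen, 1977) on the reduction of pain intensity evaluated by the VAS", with "four intervention groups; two genotypes (HbSS and HbSC) subgroups; and two repeated measures (pre- and post-intervention" measures.

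**The concern.** The primary hypothesis rests on two particular differences: combination minus tDCS alone, and combination minus PES alone. The named test is a group effect (by time) with three degrees of freedom, followed by a blanket correction. That test can be significant because, say, the combination differs from double sham, while the hypothesis itself stays unsupported.

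Two things are then left open.

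1. How strictly the two decisive comparisons are judged depends on the size of a family that the article does not define. If both must succeed, any correction between them lowers the chance of a true positive for no benefit.
2. If additive is meant as a sum of effects, the quantity that answers the question is the tDCS × PES contrast on change. The analysis does not name it.

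**Working it through.** **Inputs from the article.** Effect size 0.35, read as Cohen's f because the software is GPower and the test an ANOVA; alpha 5%; power 80%; 1:1:1:1 allocation; 128 participants, so 128/4 = 32 per intervention.

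**Assumptions added here.** f applies to pre-post change across the four arms with no genotype effect; SD of change = 1; two-sided tests; no dropout; HADS adjustment ignored; pooled error df = 128 − 8 = 120.

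**Step 1: reproduce the plan's figure.** With the noncentral F and λ = f²N:
- An omnibus test over all 8 cells (7 df) needs N = 125, or 128 as 8 × 16. At 128, λ = 0.1225 × 128 = 15.68 and power is 0.81.
- A four-group omnibus test (3 df) would need 94, and a 1-df effect 67.

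The article does not say which test was used. The 8-cell omnibus reading matches the 128. It is not a power statement for the combination-versus-single contrasts.

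**Step 2: turn f = 0.35 into arm differences.**
- Additive pattern, means (2e, e, e, 0): f = e/√2, so e = 0.35 × √2 = 0.495 SD. The combination exceeds each single arm by 0.495.
- Combination-only pattern, means (D, 0, 0, 0): f = D√3/4, so D = 0.35 × 4/√3 = 0.808 SD.

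**Step 3: power against the single arms.** One contrast has SE = √(2/32) = 0.25, so its noncentrality is 0.495/0.25 = 1.98 or 0.808/0.25 = 3.23. Single-contrast power comes from the noncentral t on 120 df. Joint power comes from 200,000 simulated trials, which keep the correlation created by the shared combination arm.

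| Alpha per test | Additive: one contrast | Additive: both | Combination-only: one contrast | Combination-only: both |
|---|---|---|---|---|
| 0.05 | 50% | 34% | 89% | 82% |
| 0.05/2 | 39% | 23% | 83% | 73% |
| 0.05/3 | 33% | 18% | 79% | 67% |
| 0.05/6 | 25% | 12% | 71% | 57% |

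With two comparisons, joint power falls by 34 − 23 = 11 points (additive) or 82 − 73 = 9 points (combination-only). With six it falls by 22 or 25 points.

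**Step 4: why no correction is needed if both must win.** If the combination is no better than at least one single technique, a false claim requires that particular test to reject. That happens at most 5% of the time when it is run at 5%. Requiring the second test as well can only lower the rate.

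**Step 5: the tDCS × PES contrast.** On change, it is (combination − tDCS alone) − (PES alone − double sham).
- SE = √(4/32) = 0.354, so the 95% CI half-width is 1.98 × 0.354 = 0.70 SD.
- Power for an interaction of 0.808 SD is 62%.
- For 0.7 SD, 80% power needs 4 × ((1.96 + 0.84)/0.7)² ≈ 64.1, so 65 per intervention or 260 in total.

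**Step 6: factorial main effects (64 vs 64).** SE = √(2/64) = 0.177.
- Additive pattern: the effect is 0.495 and power is 79%.
- Combination-only pattern: the effect is 0.808/2 = 0.404 and power is 62%. That is below the 71% for one combination-versus-single test corrected over six.

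**The case against.** The strongest reply is that the stated analysis suits the stated objective. The Primary objective, the Hypothesis and the Sample size section all ask whether the combination beats single use, and corrected group comparisons after the ANOVA address that. The additive wording comes mainly from the pitfalls section, and the Introduction uses sum and synergy loosely. The interaction also lies within the planned group-by-time effect, so it can be extracted without changing the model. **This stands.** A reader might infer that the trial cannot answer its main question at all. The documents do not support that: they support only that the relevant contrasts are not named.

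A reader might also infer that Bonferroni runs over all six pairs and is pure waste. Neither is stated. The family is undefined, so six is one end of a range. The correction is superfluous only under a both-must-win rule, which the article does not state. If a win over one technique, or over sham alone, may be reported as a finding, the correction does control error.

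Third, recoding to crossed factors is no general rescue. Main effects gain power only if effects really add, and they do not test superiority of the combination. An interaction CI of ±0.70 SD is wider than the single-technique effect assumed under additivity (0.495 SD).

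Finally, this is a condensed article, and the comparison family may be set out in an unseen SAP. **This stands in part.** The point therefore does not rest on missing detail. It rests on what the section does fix: one four-level factor and a blanket correction, for a factorial design with a two-contrast hypothesis.

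**Conclusion.** The point holds in a limited form. The analysis is valid for group differences but poorly aimed: it names neither the two contrasts behind the primary hypothesis nor the contrast that a sum-of-effects reading of additivity would need. If superiority means beating both single techniques, Bonferroni between those tests costs 9 to 11 points of joint power with two comparisons and 22 to 25 points with six, with no gain in protection for that claim.

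These sizes depend on the assumptions listed with the inputs, and above all on f = 0.35 applying to change. Even uncorrected, joint power is only 34% under the additive pattern, so the correction is not the only limit on the claim. The interaction cannot establish additivity at this sample size. The change is worth making before analysis; nothing here invalidates the design.

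**What to change.** 1. Pre-specify two contrasts on pre-post change: combination vs tDCS alone, and combination vs PES alone. Claim superiority only if both favour the combination with p < 0.05, with no correction between them. If the sham comparison in the Primary objective is part of the claim, add combination vs double sham under the same rule.
2. Keep Bonferroni for all other comparisons, and list them.
3. Say what additive means. Report the tDCS × PES (× time) contrast with its 95% CI as an estimate of departure from additivity, and state that a non-significant result does not show additivity.
4. Restate power for the two contrasts jointly. Factorial main effects are optional and should not stand in for the superiority test.

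**Cost.** Analysis wording only: the same data and the same model, with named contrasts. The trial gives up any superiority claim based on beating just one technique, and the interaction estimate will be imprecise.

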### Ethical aspects

Volunteers will receive explanation regarding their participation and the freedom to remove consent at any time during the study. They will read and receive answers to any questions before signing an Informed Consent Form (ICF), prepared according to Resolution 466/2012 of the Brazilian National Council of Health. This study has been approved by the Ethics and Research Committee (ERC) of the Adventist Institution of Bahia (CAAE No. 31237514.1.0000.0042). The study is registered at the Protocol Registration and Results System (PRS), trial number NCT02813629. Any changes in the study protocol will be informed to both the ERC and the PRS.

## Stepwise procedures

Study procedures will occur in 2 independent days (Figure 2).

**Figure 2 F2:**
[figure not shown]
Timeline and duration of study procedures.

*Day 1: Enrollment procedures*. A trained research assistant will visit SCD reference centers and health clinics to interview potential eligible subjects. Subjects interested in the study will receive detailed information about all procedures and duration of the study. Those willing to participate will be screened for eligibility criteria (40 min). Eligible subjects will receive the ICF to read. The assistant research will read aloud the ICF if requested by the subject. All doubts will be clarified and the ICF will be filled out and signed. Participants will be scheduled for data collection in the Clinical Electrophysiology Laboratory at the Federal University of Bahia.

*Day 2: Data collection*. Procedures will begin in the morning. Upon arrival of participant at the study room, an allocation envelope will be opened to determine participant's intervention group. Data collection will be divided into four stages (sample characterization, baseline assessment, intervention, and post-intervention assessment).

*Stage 1* (Sample characterization) will last ~40 min. The researcher will explain to the participant why and how to fill the socio-demographic and clinical questionnaires. The researcher will be available to clarify any doubts and help participant, if requested;*Stage 2* (Baseline assessment). EEG data will be collected during resting and Kinesthetic–MI conditions. Subsequently, in another room, the participant will receive instructions for the TMS cortical mapping. Following these electrophysiological assessments, a blood sample will be collected for BDNF and TNF serum level analysis. Finally, the pain intensity will be assessed. This stage may last up to 1 h and 30 min;*Stage 3* (Intervention). At this stage, the participant will be seated and the researcher will position the tDCS electrodes on the scalp according to the 10/20 EEG system. Electrodes will be fixed with an elastic band, comfortably adjusted. The PES electrodes will be positioned at the most painful hip. This stage will last around 40 min;*Stage 4* (Post-intervention assessment). In the last part of the study, the sequence of assessments will be slightly different from Stage 2. First, pain intensity will be measured. Then, a blood sample will be collected. Blood sample must be collected earlier in this stage to reduce circadian cycle effect on BDNF and TNF serum levels (Pan et al., 1985; Begliuomini et al., 2008). Finally, EEG data and TMS cortical mapping will be collected. The final stage is expected to last up to 1 h and 30 min.

Participants may take 5–10 min-breaks between all stages. During their time in the laboratory room, participants will have snacks and light beverage available at breaks. Participants will be reimbursed for transportation costs and receive a food voucher at the end of data collection.

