## Methodology

### Study design, description of allocation, and blinding

This is a clinical, parallel, controlled, block-randomized, double blind trial. The study will occur in 2 days at the Clinical Electrophysiology Laboratory of the Federal University of Bahia, Brazil. An assistant researcher not involved in any other stage of the study will generate an allocation sheet (www.randomization.com) creating four groups for each SCD genotype (HbSS and HbSC), totaling eight experimental groups. Allocation concealment will be enforced using sealed opaque envelopes listed in ascending order, and the allocation secrecy will be maintained until the end of the analyses. The allocation envelope will be opened on the day of the intervention according to the order of inclusion of the study participant. The envelope will contain one of the following interventions: (1) active tDCS + active PES (*n* = 16); (2) active tDCS + sham PES (*n* = 16); (3) sham tDCS + active PES (*n* = 16); (4) sham tDCS + sham PES (*n* = 16) (Figure 1). These interventions will be tested either in the HbSS (*n* = 64), and HbSC (*n* = 64) groups, totalizing 128 participants.

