#### Discontinuity

Moderate adverse effect (i.e., discomfort enough to interfere with patient's usual activities) or severe (i.e., significant impairment of the patient's usual activities or even total disability, and life threatening) during neurophysiological evaluation or intervention;Participant withdraws consent at any stage of the study.

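### The allocation envelope is opened on arrival, up to about 130–140 minutes before baseline pain is recorded, so baseline data may be collected by staff who know the arm and allocations can be used up before treatment

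*Protocol article*

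**What the plan says.** Three parts of the protocol article bear on this.

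- **Timing of allocation.** Under Study design, description of allocation, and blinding: "The allocation envelope will be opened on the day of the intervention according to the order of inclusion of the study participant". That sets the day but neither the hour nor the person. Stepwise procedures, Day 2, sets the hour: "Upon arrival of participant at the study room, an allocation envelope will be opened". The four data-collection stages come afterwards.
- **Order of the stages.** Stage 1 takes about 40 min and includes the HADS. Stage 2 runs through EEG, TMS mapping and a blood sample, and then "Finally, the pain intensity will be assessed". On its length: "This stage may last up to 1 h and 30 min". Stimulation is Stage 3. In addition, "Participants may take 5–10 min-breaks between all stages".
- **Leaving the study.** The Discontinuity section allows withdrawal of consent at any stage. It also allows discontinuation for moderate or severe adverse effects "during neurophysiological evaluation or intervention".

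On blinding, the design section calls the trial double blind and adds that "the allocation secrecy will be maintained until the end of the analyses". The measures described protect participants (Interventions; Potential intervention biases) and analysts (Statistical analysis). None is described for the staff who take the baseline measurements.

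**The concern.** Randomisation is normally revealed as late as practicable, after baseline is fixed. Here it is revealed before any Day 2 measurement, and no step in Stages 1 or 2 needs the arm. Two things follow.

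1. **Possible exposure of baseline data.** Stepwise procedures uses the same term, the researcher, for the person who explains and helps with the Stage 1 questionnaires and for the person who places the Stage 3 tDCS electrodes. If this is one person who has seen the envelope, the baseline measures are taken with knowledge of the arm. The HADS is the adjustment variable in all analyses, and baseline VAS is half of the primary pre–post comparison. Influence at that stage cannot be undone in the analysis.

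2. **Allocation without treatment.** Up to about two and a half hours of testing lie between allocation and stimulation. Someone who leaves in that window is already allocated but contributes neither treatment nor a post-intervention VAS. The Sample size section makes the computed 128 the enrolment target, with no stated allowance for loss.

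**Working it through.** **Step 1. Check that the stage times fit the stated visit length.**
- Stages 1 to 4 are 40, up to 90, about 40 and up to 90 min: 40 + 90 + 40 + 90 = 260 min.
- Three breaks of 5–10 min add 15–30 min, giving 275–290 min.
- This agrees with the Abstract's total of about 5 h, so the stage times can be used.

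**Step 2. Interval from envelope to baseline pain.** Baseline pain is the last item of Stage 2, so the interval is Stage 1 + any break + Stage 2.
- No break: 40 + 90 = 130 min.
- One break: 40 + 5 + 90 = 135 min, to 40 + 10 + 90 = 140 min.
- The 90 min is an upper limit, so these are upper figures under the stage times.
- The component times under Secondary outcome measures (EEG about 60, TMS mapping about 40, blood under 5 min) sum to about 105 min, more than the 90 allowed. On those times the interval is 40 + 105 = 145 min, or 150–155 min with a break. The stage limits are therefore not an exaggeration.

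**Step 3. Interval from envelope to Stage 3.** With up to two breaks: 40 + 90 = 130 min, to 40 + 90 + 2 × 10 = 150 min. Loss after allocation but before treatment can occur in this window.

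**Step 4. Does anything before Stage 3 need the arm?** Stage 1 is questionnaires. Stage 2 is EEG, TMS mapping, blood and pain. All are described identically for every participant. The arm first matters when stimulation is delivered.

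**Step 5. Room for loss in the sample size.**
- Four arms × two genotypes × 16 = 128, and enrolment stops at the same 128.
- The article does not say which GPower routine was used. Reading 0.35 as Cohen's f in a fixed-effects ANOVA over 8 cells (an assumption) gives λ = f²N = 0.1225 × 128 = 15.68 on 7 and 120 df, with power 0.814. The smallest balanced N reaching 80% is 128, so this reading reproduces the stated size.
- Illustration only, with hypothetical loss rates after allocation from any cause:

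| Loss after allocation | N analysed | λ | Power |
|---|---|---|---|
| 0% | 128 | 15.68 | 0.814 |
| 5% | 121.6 | 14.90 | 0.789 |
| 10% | 115.2 | 14.11 | 0.760 |
| 20% | 102.4 | 12.54 | 0.695 |

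The table shows that there is little slack. It does not predict how many participants will be lost during baseline testing.

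**Step 6. After the change.** If the envelope is opened once baseline VAS is recorded, at the start of Stage 3, both intervals fall to zero and the required 128 is unchanged.

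**The case against.** The case on the other side is substantial, and much of it stands.

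- **The opener is not named.** A reader might infer that baseline data are in fact collected with the arm known. The article does not say so. The sentence is passive, a physical therapist is put in charge of the intervention, and the trial is described as double blind. The text supports only that no separation is described and that exposure is possible.
- **No contradiction with the secrecy statement.** A reader might also set early opening against the promise of secrecy to the end of the analyses. But somebody must learn the arm to deliver it, and opening at Stage 3 would conflict just as much. Secrecy depends on who learns the arm. Early opening leaves the promise less well supported but does not break it.
- **Enrolment is safe.** Screening and consent are completed on Day 1, so the revealed arm cannot steer who enters.
- **The routes of influence are indirect.** The HADS and VAS are the participant's own ratings, and participants are kept unaware of the arm. EEG artefact rejection is offline with fixed limits, and the motor threshold uses a set criterion and an adaptive tool. Each secondary outcome has its own baseline, so baseline VAS bears on the pain comparison and not on every analysis.
- **Loss costs numbers more than validity.** Dropout before treatment among participants unaware of their arm should not differ by arm. The discontinuation rule also covers the post-intervention evaluation, so not every such loss precedes treatment.

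What survives is the timing. The envelope is opened early for no stated purpose. Later opening protects the baseline measures whoever opens it, and it removes the allocated-but-untreated category whatever the reason for leaving.

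**Conclusion.** The point holds as one of sequence and should be fixed. It does not invalidate the design. Allocation is revealed up to 130–140 min before baseline pain and 130–150 min before stimulation, on the article's own stage limits. Baseline HADS, EEG, TMS and VAS may be collected by staff who know the arm. Participants who stop during baseline testing use an allocation without treatment or outcome, and no allowance is stated for them.

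Two sizes cannot be given. The documents offer no basis for the amount of any assessor influence. They also give no dropout rate, so attaching a percentage to 128 and reporting a head count would be guesswork. The power figures above rest on an assumed reading of the effect size and on hypothetical loss rates.

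**What to change.** Amend Stepwise procedures, Day 2, in three respects:

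1. Open the envelope only after Stage 2 is complete and baseline VAS has been written down, at the start of Stage 3.
2. State that participants who withdraw or are discontinued before that point are not randomised and use no envelope.
3. Where existing staffing allows, have the therapist who delivers the stimulation open the envelope, out of sight of those who assess Stages 1, 2 and 4.

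Items 1 and 2 need no extra staff, visit or participants, and they remain within the design section's rule that the envelope is opened on the intervention day. Item 3 may need a second person if one researcher now does everything. It is also the only item that bears on blinding of the post-intervention assessor, which the timing change leaves as it is. The cost is a short procedural amendment, notified to the ethics committee and the registry as Ethical aspects requires. Late opening does not prevent people from leaving during baseline or after stimulation begins; it ensures only that those who leave during baseline have not already been allocated.

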The stimulus intensity for mapping will be set at 120% of Active Motor Threshold (AMT) for the *gluteus maximus* muscle. AMT will be the minimum intensity at which a TMS stimulus evokes a response of 200 μV while the *gluteus maximus* muscle is contracted under a comfortable bridge position in supine. Then, the AMT will be determined using the adaptive TMS motor threshold assessment tool (MTAT 2.0). The TMS pulse will be applied every 6 s, with a total of five stimuli at each site on the 8 × 7 cm grid.

Surface electrodes Ag/AgCl (3M, USA) will be used to record EMG activity at the *gluteus maximus* muscles, bilaterally. The two registering electrodes will be placed at 50% on the line between the second sacral vertebrae (S2) and the hip greater trochanter. The positioning of the electrode will be determined after palpation of the *gluteus maximus* muscle during a moderate voluntary contraction. The reference electrode will be placed over the hip greater trochanter or S2 (Fisher et al., 2013). The EMG signals will be amplified 3,000 times, filtered, bandpassed between 1 Hz and 2 kHz, with sampling rate maintained at 4 kHz using Signal v.06 software (Cambridge Electronic Design, UK). EMG data elicited by TMS will be monitored in real time to ensure the consistency of evoked responses (Signal, Cambridge Electronic Design, UK). Mapping of the *gluteus maximus* muscle will take ~40 min.

TMS map volume and center of gravity (CoG) of both *gluteus maximus* muscles will be used as dependent variables. These parameters will be calculated, respectively, by the sum of normalized MEP amplitudes at each site and by the formula:

$$\text{CoG}=\sum {\text{V}}_{\text{iX}}{\text{X}}_{\text{i}}/\sum {\text{V}}_{\text{i}};\sum {\text{V}}_{\text{iX}}{\text{Y}}_{\text{i}}/\sum {\text{z}}_{\text{i}}$$

Where, V_i_ = mean MEP amplitude at each site with the coordinates X_i_, Y_i_

C. Serum levels of BDNF and TNF

Serum levels of BDNF and TNF will be measured pre- and post-intervention. Approximately 5 mL of blood will be collected from each study participant and stored in test tubes with anticoagulant EDTA (0.03%). This procedure will last <5 min. The blood sample will be centrifuged at 2,500 rpm for 10 min and the plasma stored at a temperature of −40°C.

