### Measurement biases

*Gluteus maximus* muscle TMS mapping may be difficult because of its small and deep representation in the primary motor cortex. We aim to counteract this problem using active motor threshold and contraction during TMS assessment, a method successfully used by others (Lepley et al., 2013; Te et al., 2017). Neuronavigated TMS could further help with this measurement problem, but this resource is not available at the study laboratory. Nonetheless, the original study to validate TMS cortical mapping of the *gluteus maximus* muscle used a system similar to the one available for this study (Fisher et al., 2013).

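### Baseline and post-treatment pain are rated under different conditions (after TMS mapping versus after seated rest), so any settling procedural pain can enter the pre-post drop of every arm

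*Protocol article*

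**What the plan says.** The primary outcome is VAS pain, rated seated at rest and then seated while abducting the more painful hip, before and after the intervention (Primary outcome measure).

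Under Stepwise procedures, Stage 2 runs EEG, TMS mapping, blood, pain: "Subsequently, in another room, the participant will receive instructions for the TMS cortical mapping", and then "Following these electrophysiological assessments, a blood sample will be collected for BDNF and TNF serum level analysis. Finally, the pain intensity will be assessed". Stage 4 starts the other way round: "First, pain intensity will be measured. Then, a blood sample will be collected". EEG and mapping follow. The article acknowledges the changed order, but the only reason it gives concerns circadian effects on the blood markers.

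On what precedes each rating:
- **Baseline.** Mapping takes about 40 min. The active motor threshold is found while the "muscle is contracted under a comfortable bridge position in supine" (Secondary outcome measures, TMS cortical mapping). The Measurement biases section describes "using active motor threshold and contraction during TMS assessment". The blood draw between mapping and the rating lasts under 5 min.
- **Post-treatment.** The participant sits quietly for 30 min of stimulation (Interventions; Potential intervention biases), within a stage of about 40 min.

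The Potential confounders section names only anxiety and depression for pain intensity.

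**The concern.** Every participant has chronic pain from hip osteonecrosis, and the mapping uses active contraction of a hip extensor. If this provokes pain that fades during the seated intervention, the baseline rating is raised and the post-treatment rating is not. The pre-post change then combines the treatment response with recovery from the test procedure.

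Two things are at stake. First, the time effect and each arm's own pain reduction could look like analgesia when part of it is recovery. This matters for interpretation because the Sample size section words the hypothesis as a treatment that "reduces pain intensity by a large percentage as opposed to use of isolated tDCS or PES", and the Introduction compares percentage reductions from an earlier study. Second, a flare that differs between patients and enters only one of the two ratings adds variance to the change on which the group-by-time test rests.

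**Working it through.** **1. Mapping time.** Inputs from TMS cortical mapping: five stimuli per site, one every 6 s, on an 8 × 7 cm grid. Spacing of 1 cm is assumed.
- 56 cells: 56 × 5 × 6 s = 1,680 s = 28 min.
- 72 intersections (9 × 8): 72 × 5 × 6 s = 2,160 s = 36 min.

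With set-up and threshold finding, both agree with the stated 40 min or so.

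**2. Effect of a common flare on the arms.** Let the flare add *c* points to the baseline rating and be gone by the post-treatment rating. Each arm's drop is then its true drop plus *c*. Assume true drops of 1.5 / 0.75 / 0.75 / 0 points (combined, tDCS alone, PES alone, double sham).

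| *c* | Observed drops | Combined − tDCS alone | Combined − double sham |
|---|---|---|---|
| 0 | 1.5 / 0.75 / 0.75 / 0 | 0.75 | 1.5 |
| 1 | 2.5 / 1.75 / 1.75 / 1.0 | 0.75 | 1.5 |
| 2 | 3.5 / 2.75 / 2.75 / 2.0 | 0.75 | 1.5 |

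The contrasts do not move. Simulation with these inputs gave the same result.

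**3. Within-arm drop in double sham.** Assume 32 per arm (16 in each genotype), a change SD of 2 and no treatment effect. The chance of a significant paired drop (noncentral t, two-sided 5%) is 28% at *c* = 0.5, 78% at *c* = 1 and 98% at *c* = 1.5. For *c* = 1 it runs from 96% (SD 1.5) to 59% (SD 2.5).

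**4. Percentage reductions.** Assume a true pain level of 5, flare *m* and true reduction *e*. Apparent reduction = (5 + *m* − 5(1 − *e*)) / (5 + *m*).

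| *m* | *e* = 0 | *e* = 15% | *e* = 36.5% | Gap between the last two |
|---|---|---|---|---|
| 0 | 0% | 15% | 36.5% | 21.5 points |
| 0.5 | 9% | 23% | 42% | 19.5 points |
| 1.0 | 17% | 29% | 47% | 17.9 points |
| 1.5 | 23% | 35% | 51% | 16.5 points |

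The 15% and 36.5% are the earlier study's figures for tDCS alone and for the combination (Introduction). They serve here only as examples.

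**5. Noise.** If the flare varies between patients independently of the change it is added to, variance inflation = (SD_change² + SD_flare²) / SD_change².
- Change SD 2.5, flare SD 0.5: 6.50 / 6.25 = 1.04.
- Change SD 2.0, flare SD 1.0: 5 / 4 = 1.25, as if 128 / 1.25 ≈ 102 participants had been enrolled.
- Change SD 1.5, flare SD 1.0: 3.25 / 2.25 = 1.44.

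In the middle case the standard error of a two-arm contrast with 32 per arm rises from √(2 × 4 / 32) = 0.50 to √(2 × 5 / 32) = 0.56.

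**The case against.** The strongest reply is that the trial asks whether the combination beats single or sham stimulation, and the double-sham arm is there to absorb non-specific pre-post change. This stands. A reader might infer from the unequal order that the arm comparison is biased. The article does not support that: the order is the same in every randomised arm, and an additive flare cancels in expectation.

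Three other stronger readings also fail.
- **Floor effect.** A reader might expect a falling sham arm to leave too little room above zero. A flare that has settled raises only the baseline and leaves every post-treatment score where it was.
- **Sustained bridge.** The article gives the bridge only for the motor threshold and calls it comfortable. For the mapping it supports contraction, with the participant lying comfortably supine. It gives no load or duration of contraction.
- **Demonstrated flare.** No hip pain from mapping is reported, and the TMS risks listed under Potential adverse effects do not include it.

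It can also be said that the Statistical analysis section names no percentage-change endpoint, so the percentage figures affect interpretation rather than a planned test. That is right. Finally, rating pain last before and first after treatment brackets the intervention closely and keeps mapping out of the interval. That is a real merit, and the fix should keep it.

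What remains is that the two primary-outcome ratings follow different conditions and the article does not discuss the effect on pain.

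**Conclusion.** The concern holds in a limited form. Procedural pain that settles can be counted in the pre-post drop of every arm. It can inflate the time effect and the within-arm and percentage reductions. If it varies between patients, it adds avoidable noise to the group-by-time test, with variance inflation of about 4% to 44% over the assumed SDs. The expected group-by-time contrast is unbiased, provided that the flare is additive and settles equally in all arms.

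Flare size, flare SD, change SD and resting pain level are all assumptions, because the article gives none of them. The order and durations of the assessments are as stated there. This is a cheap improvement to a primary measurement, not a flaw that invalidates the design.

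**What to change.** 1. Take the analysis baseline VAS, in both positions, in Stage 3 with the participant seated, immediately before the current starts.
2. Keep the rating at the end of Stage 2. It gives continuity with participants already enrolled, and the difference between the two ratings measures any flare directly.
3. State that efficacy conclusions come from the group-by-time contrasts, not from the time effect or within-arm drops.

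Costs:
- A second rating takes a few extra minutes.
- Hip abduction has to be done with electrodes fitted, or the rating taken just before they are fixed.
- The definition of baseline changes part-way through enrolment and needs an indicator in the analysis.
- Stage 3 lasts about 40 min with 30 min of stimulation, so 40 − 30 = about 10 min of seated set-up precedes the new rating, against 30 to 40 min before the post-treatment one. The mismatch is reduced, not removed.
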